**Methods:**

The study will be conducted as a prospective, cluster-randomised controlled trial using a stepped-wedge design. STATAMED wards will be implemented at six hospital sites, and the catchment areas will be divided into clusters. All referring entities in a catchment area—including general practitioners (GPs), office-based specialists, nursing homes, ambulatory care services, and emergency services—will be potential candidates for cluster formation. The intervention group is expected to consist of 4481 patients. Primary and secondary outcomes will be assessed using claims data from participating statutory health insurers. A health economic evaluation will also be conducted using these data to compare costs associated with STATAMED and usual care. To minimise the risk of bias, analyses will be conducted on both an intention-to-treat and actual treatment basis.

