**Fig. 1 Fig1:**
[figure not shown]
Study design

The intervention group consists of all eligible patients (see the “Eligibility criteria {10}”) treated in the STATAMED wards. Eligible individuals must be covered by one of the participating statutory health insurers and meet the eligibility criteria. Claims data will only be provided for individuals insured by one of the participating statutory health insurers.

Additionally, three control groups are planned:Control group 1 consists of patients who meet the eligibility criteria for treatment in a STATAMED ward but receive usual hospital care at a non-STATAMED hospital because their referring entity is located in a cluster assigned to the control phase at the time of treatment. This is the standard control group in the stepped-wedge design, enabling the analysis of each cluster before and after STATAMED is introduced.Control group 2 consists of patients who meet the eligibility criteria for treatment at a STATAMED ward and whose referring entity is located in a cluster assigned to the intervention phase at the time of treatment but who are referred to and receive treatment at a non-STATAMED hospital. This group allows for the examination of possible selection effects (i.e. patients who prefer usual hospital care over STATAMED).Control group 3 consists of patients who meet the eligibility criteria for treatment at a STATAMED ward but whose referring entity is located outside a participating hospital site’s catchment area, resulting in treatment at a non-STATAMED hospital. This group allows for the consideration of additional spatial effects. Figure 2 illustrates the various control groups.

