### Eligibility criteria {10}

#### Inclusion criteria for patients

Patients are eligible for inclusion if they meet the following criteria: They present at a participating referring entity with a general medical condition requiring inpatient treatment as defined by the German Appropriate Evaluation Protocol (G-AEP), have a diagnosis corresponding to an ICD-10 code designated specifically for this project (i.e. conditions relevant to the trial), and are expected to have an uncomplicated course of disease corresponding to a patient clinical complexity level (PCCL) of 0 to 2. Additionally, patients must be at least 18 years of age.

The following list of ICD-10-GM (2023) codes includes exemplary diagnoses relevant to the study but is not exhaustive:I10.01 (benign essential hypertension: with mention of hypertensive urgency)I48.1 (persistent atrial fibrillation)E86 (volume depletion)K59.09 (other and unspecified constipation)I50.14 (left ventricular failure: with symptoms at rest)I20.8 (other forms of angina pectoris)I48.0 (paroxysmal atrial fibrillation) and R55 (syncope and collapse)R07.3 (other chest pain) and K29.6 (other gastritis)N39.0 (urinary tract infection, site not specified)I50.13 (left ventricular failure: with symptoms under mild strain)J20.9 (acute bronchitis, unspecified)J18.9 (pneumonia, unspecified)I50.01 (secondary congestive heart failure)K57.32 (diverticulitis of large intestine without perforation, abscess, or bleeding)E11.91 (type 2 diabetes mellitus: without complications, uncontrolled)R10.3 (pain localised to other parts of lower abdomen)A09.9 (gastroenteritis and colitis of unspecified origin)K29.1 (other acute gastritis)

The complete list of ICD-10 codes can be provided upon request.

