#### Eligibility criteria for referring entities

Referring entities, including GPs, office-based specialists, nursing homes, ambulatory care services, and emergency services, must complete mandatory training on STATAMED-specific processes, such as the case review process, prior to participation. Additionally, they must sign a participation agreement to be authorised to refer patients to STATAMED wards.

Participation is voluntary and may be discontinued at any time. Referring entities that choose to withdraw from the project may cease referring patients to STATAMED wards without further consequences. They may also revoke consent for the use of their practice-related data in the scientific evaluation, in accordance with applicable data protection regulations. In the event of withdrawal, the health insurer leading the project consortium should be notified to ensure accurate documentation and appropriate adjustments to recruitment planning.

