### Recruitment {15}

Participant recruitment will be carried out by the referring entities in the catchment area of each participating hospital site. To achieve the target sample size, a sufficient number of referring entities must be involved. Therefore, the lead STATAMED physician at each intervention site is responsible for establishing a local network of referring entities to support recruitment. Lead STATAMED physicians will contact potential referring entities individually and inform them about the project. In addition, information events will be held, and public outreach (e.g. press releases, radio and TV interviews, and social media campaigns) will be used to raise general awareness of the project.

Referring entities must sign a contract to participate in STATAMED and obtain authorisation to refer patients. There is no minimum number of referring entities required per hospital as local conditions (e.g. population size and physician density) vary across sites. Each hospital is expected to recruit a sufficient number of referring entities to ensure that the required sample size is reached.

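### The protocol does not settle whether control patients need a participating referring entity, so control group 2 cannot isolate patient preference as stated

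*Protocol article*

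**What the plan says.** Under Eligibility criteria {10}, the first inclusion criterion for patients is: "They present at a participating referring entity with a general medical condition requiring inpatient treatment". The section on referring entities says what participation takes: entities "must complete mandatory training on STATAMED-specific processes", and "they must sign a participation agreement to be authorised to refer patients to STATAMED wards". It adds: "Participation is voluntary and may be discontinued at any time".

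Recruitment {15} places this activity inside the catchment areas: "Participant recruitment will be carried out by the referring entities in the catchment area of each participating hospital site". It also says: "There is no minimum number of referring entities required per hospital", because local conditions differ, and expects each hospital to enlist enough entities to reach the sample size.

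Clusters are not restricted to entities that have joined. The abstract says that all referring entities in a catchment area "will be potential candidates for cluster formation", and Trial design {8} divides the areas by postal code.

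Trial design {8} defines all three control groups as patients who satisfy the eligibility criteria. Control group 2 adds that the referrer is located in an intervention-phase cluster and that treatment took place at a non-STATAMED hospital. Control group 3 has referrers outside the catchment area. The stated purpose of control group 2 is: "This group allows for the examination of possible selection effects (i.e. patients who prefer usual hospital care over STATAMED". Concealment mechanism {16b} says that controls are found retrospectively from ICD-10 codes in claims data. It mentions neither the referrer's participation nor any offer or refusal.

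**The concern.** A patient whose practice has not signed cannot be referred to a STATAMED ward. If that practice lies in an intervention-phase cluster, the patient enters control group 2 on location and diagnosis without having expressed any preference. The protocol would still count that patient as someone who preferred usual care.

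The interpretation is at stake. Entities are enlisted through a network built by each lead physician, so those that sign may differ from those that do not. A difference between the intervention group and control group 2 could then be an effect of which practices joined, reported as an effect of patient choice. A null result would not rule out preference effects either. Matching on age, gender and morbidity, the variables named under Statistical methods {20a}, does not separate the two. If control group 2 also enters the intention-to-treat comparison, the unsettled criterion decides who is counted there.

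**Working it through.** The protocol states no figure on this point, so none can be reproduced. The check sets the passages side by side and then adds an illustration.

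**Reading A: the participating-entity criterion binds controls.**
- Control group 2 is limited to patients of signed entities, so patients of unsigned entities drop out of it.
- Control group 3 needs signed entities outside the catchment areas. Recruitment {15} describes none there, so the group is essentially empty.

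**Reading B: the criterion does not bind controls.**
- Control group 3 can be formed.
- Control group 2 takes in patients of unsigned entities, and the preference statement is wrong for them.

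Reading A breaks control group 3, and Reading B breaks the stated meaning of control group 2. The way clusters are formed (all entities, by postal code) and controls are found (ICD-10 codes in claims) points towards B. Concealment mechanism {16b} and Implementation {16c} also describe access by the entity's cluster alone, without mentioning the signed agreement.

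**Illustration under Reading B.** Let *s* be the share of eligible patients in intervention-phase clusters whose entity has signed, and *q* the share of those patients who are treated elsewhere. Both are assumptions, since the protocol gives neither.

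Share of control group 2 from unsigned entities = (1 − s) / [(1 − s) + s·q]

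With q = 0.5:
- s = 0.3: 0.70 / (0.70 + 0.15) = 82%
- s = 0.6: 0.40 / (0.40 + 0.30) = 57%
- s = 0.8: 0.20 / (0.20 + 0.40) = 33%
- s = 0.9: 0.10 / (0.10 + 0.45) = 18%

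At q = 0.5 the share falls below one half once 1 − s < 0.5·s, that is, once s > 2/3.

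The result also depends on q:
- s = 0.6, q = 0.8: 0.40 / (0.40 + 0.48) = 45%
- s = 0.3, q = 0.3: 0.70 / (0.70 + 0.09) = 89%
- s = 0.7, q = 0.3: 0.30 / (0.30 + 0.21) = 59%

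The complement (11% and 41% in the last two lines) is an upper limit on the patients who truly preferred usual care, because it counts everyone treated elsewhere from a signed entity as a preferrer. The unsigned share is zero only at s = 1, which the protocol does not require.

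**The case against.** Four objections carry weight.

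- **The text does invoke eligibility.** A reader might infer that control group 2 leaves out the participating-entity criterion. The documents do not say so: the definition requires the eligibility criteria and adds location to them. This stands. The fault is a conflict between passages, not an express omission. It does not rescue the plan, because the same literal reading empties control group 3.
- **Control group 2 is not useless, nor the only safeguard.** A reader might infer that it can show nothing about selection, or that nothing else addresses selection. Neither is supported. The group can show referrer and patient selection combined, and the protocol also plans matching and both intention-to-treat and per-protocol analyses. A location-based group has a proper use as well, since a cluster-level intention-to-treat analysis needs the eligible patients of unsigned entities. What the group cannot do is isolate preference.
- **The size is unknown.** A reader might infer that most of control group 2 comes from unsigned entities. That holds only for part of the assumed range.
- **This could be left to an analysis plan.** How the group is split could be. The incompatible eligibility statements and the asserted interpretation stand in the protocol itself and would remain there.

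It is also fair to say that control group 1 is named as the standard stepped-wedge comparator, so the confirmatory comparison does not hang on this point alone.

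**Conclusion.** The point holds as a conflict between the inclusion criteria, the rules for referring entities, the description of recruitment, the way controls are identified, and the control-group definitions. As written, either control group 3 is essentially empty, or control group 2 mixes entity participation with patient selection and cannot bear the preference interpretation put on it. The conflict follows from the text and needs no assumption. Its size does: with half of signed-entity patients treated elsewhere, the unsigned share of control group 2 runs from 82% to 18% as signed coverage goes from 30% to 90%, and the documents do not place the trial in that range. The protocol should be corrected. The correction is cheap and can be made before the final data delivery, expected around January 2027.

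**What to change.** 1. State that the participating-entity criterion governs admission to STATAMED only. Give claims-identified controls in all three groups an eligibility rule that claims data can apply and that they can meet.
2. Keep the whole location-based control group 2 for any cluster-level intention-to-treat analysis.
3. For the selection question, split it by the referrer's status on the admission date: 2a (entity authorised to refer) and 2b (entity not authorised). Report the two separately, 2b as bearing on entity participation.
4. Reword the purpose of control group 2. Even 2a mixes patient preference with the referrer's own choice, refusal at case review and lack of ward capacity, because no offer or refusal is described for controls. The matching phrase under Statistical methods {20a} needs the same qualification.
5. Do not rely on a comparison that restricts control group 1 to entities that later sign. That conditions on a voluntary choice which may follow randomisation. If it is wanted, label it an exploratory sensitivity analysis.

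**Cost.** Table 1 already lists identification numbers and postal codes of referring entities, for assigning patients to clusters. It lists no contract date, so a date of authorisation, and of withdrawal where it occurs, must be obtained and linked for each entity. Group 2a is smaller than control group 2, so its estimates are less precise. The rest is wording.

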**Fig. 2 Fig2:**
[figure not shown]
Intervention groups and control groups. Notes: IG—intervention group, CG_1—control group 1, CG_2—control group 2, CG_3—control group 3, *transition phase,** follow-up

## Methods: participants, interventions, and outcomes

### Study setting {9}

STATAMED will be implemented at six hospital sites across Germany, with three located in rural areas and three in urban areas. The list of study sites can be found in the registry (DRKS00033096).

The six sites consist of small- and medium-sized hospitals, with the smallest having 15 beds and the largest 229 beds. The sites also vary in other characteristics, such as the number of wards present in addition to the STATAMED ward and whether the hospital has an emergency department. This information is available to the evaluators and will be taken into account during the analysis.

Data for the control group will be obtained from patients who receive treatment at non-STATAMED hospitals. These may be any hospital that is allowed to treat patients who are covered by statutory health insurance (see also “Explanation for the choice of comparators {6b}”).

### Eligibility criteria {10}

#### Inclusion criteria for patients

Patients are eligible for inclusion if they meet the following criteria: They present at a participating referring entity with a general medical condition requiring inpatient treatment as defined by the German Appropriate Evaluation Protocol (G-AEP), have a diagnosis corresponding to an ICD-10 code designated specifically for this project (i.e. conditions relevant to the trial), and are expected to have an uncomplicated course of disease corresponding to a patient clinical complexity level (PCCL) of 0 to 2. Additionally, patients must be at least 18 years of age.

The following list of ICD-10-GM (2023) codes includes exemplary diagnoses relevant to the study but is not exhaustive:I10.01 (benign essential hypertension: with mention of hypertensive urgency)I48.1 (persistent atrial fibrillation)E86 (volume depletion)K59.09 (other and unspecified constipation)I50.14 (left ventricular failure: with symptoms at rest)I20.8 (other forms of angina pectoris)I48.0 (paroxysmal atrial fibrillation) and R55 (syncope and collapse)R07.3 (other chest pain) and K29.6 (other gastritis)N39.0 (urinary tract infection, site not specified)I50.13 (left ventricular failure: with symptoms under mild strain)J20.9 (acute bronchitis, unspecified)J18.9 (pneumonia, unspecified)I50.01 (secondary congestive heart failure)K57.32 (diverticulitis of large intestine without perforation, abscess, or bleeding)E11.91 (type 2 diabetes mellitus: without complications, uncontrolled)R10.3 (pain localised to other parts of lower abdomen)A09.9 (gastroenteritis and colitis of unspecified origin)K29.1 (other acute gastritis)

The complete list of ICD-10 codes can be provided upon request.

#### Exclusion criteria for patients

Patients will be excluded if they meet any of the following criteria: They require highly technical diagnostic procedures (as defined by the eligibility criteria for STATAMED wards), require inpatient surgery, or have been transferred from other hospitals.

#### Eligibility criteria for STATAMED wards

Each participating hospital site is required to ensure the availability of a defined minimum number of staff for its STATAMED ward, including 2.9 full-time equivalent (FTE) ward physicians along with frontline on-call coverage and backup coverage by a senior physician, as well as 7.5 FTE nurses. The following essential medical equipment must also be available: ambulatory ECG (e.g. Holter monitor), ambulatory blood pressure monitor, mobile X-ray unit, ultrasound unit, blood gas analyser, gastroscope, colonoscope, and basic laboratory facilities (cooperation with external providers is permissible). These staffing and equipment requirements are based on a STATAMED ward capacity of 20 beds.

Participation in the project is voluntary. However, hospitals that agree to participate and implement a STATAMED ward are contractually obliged to meet the eligibility criteria throughout the trial period. If a participating a hospital voluntarily withdraws from the project or is no longer able to meet the criteria (e.g. due to staff shortages), the funder may require repayment of the financial support provided for STATAMED personnel. This includes staff funding for the lead STATAMED physician, case manager, and mobile nurse.

Any such change in participation status must be reported immediately to the health insurer leading the project consortium and to the evaluators, who will assess the implications for ongoing trial operations and determine whether corrective measures are required (e.g. recruitment adjustments). The evaluation team will document and account for these events during the final analysis. Patient safety is ensured as STATAMED services are offered in addition to standard care.

If a STATAMED ward is no longer able to provide standard care services, all patients currently receiving treatment will be transferred to an appropriate ward or facility to ensure that their care is not disrupted.

#### Eligibility criteria for referring entities

Referring entities, including GPs, office-based specialists, nursing homes, ambulatory care services, and emergency services, must complete mandatory training on STATAMED-specific processes, such as the case review process, prior to participation. Additionally, they must sign a participation agreement to be authorised to refer patients to STATAMED wards.

Participation is voluntary and may be discontinued at any time. Referring entities that choose to withdraw from the project may cease referring patients to STATAMED wards without further consequences. They may also revoke consent for the use of their practice-related data in the scientific evaluation, in accordance with applicable data protection regulations. In the event of withdrawal, the health insurer leading the project consortium should be notified to ensure accurate documentation and appropriate adjustments to recruitment planning.

### Who will take informed consent? {26a}

Informed consent from trial participants in the intervention group will be obtained during the admission process at the STATAMED wards.

The three control groups consist of patients who meet the eligibility criteria but receive treatment at non-STATAMED hospitals. The control groups will be identified using claims data from the participating statutory health insurers. The evaluation of outcomes in the control groups will be based on routinely collected claims data, which the participating statutory health insurers provide independently of the study. The claims data will be anonymised, and no informed consent is required for these groups.

### Additional consent provisions for collection and use of participant data and biological specimens {26b}

No personal data are collected. The claims data used for this study are anonymised. No biological specimens will be collected in this trial.

### Interventions

#### Explanation for the choice of comparators {6b}

STATAMED is a new model of care that provides standard general medical treatment in a short-stay ward with approximately 20 beds, combined with various other care coordination interventions (see below). To assess its effectiveness, the hospital care provided in STATAMED wards will be compared to usual hospital care (i.e. standard general medical treatment only).

In Germany, hospital treatment is regulated by Book V of the German Social Code (SGB V). Hospital admission is restricted to cases that cannot be adequately managed by outpatient physicians. Nonemergency patients must be referred for admission by an outpatient physician. Patients insured through statutory health insurance, which covers 87.3% of the German population [36], may choose any hospital as long as the hospital is part of the state hospital plan (“Landeskrankenhausplan”), a university hospital, or has a contract with statutory health insurers (“Versorgungsvertrag”). These conditions are met by 89% of hospitals in Germany [37].

### Intervention description {11a}

STATAMED encompasses a range of interventions designed to ensure continuity of care and improve coordination between hospital and outpatient settings both before and after hospital discharge. The following interventions will be implemented:Short-stay ward: Each participating hospital site will include (or, in the case of very small hospitals, consist of) a dedicated short-stay ward (“STATAMED ward”) for patients with general medical conditions who require inpatient treatment, have a diagnosis matching a STATAMED-specific ICD-10 code, and are expected to have an uncomplicated disease course (see eligibility criteria {10}). The average length of stay in a STATAMED ward is anticipated to be approximately 3 days.Case review: To determine whether a patient is suitable for treatment in a STATAMED ward, a mandatory case review will be conducted between the referring physician and the lead STATAMED physician of the respective STATAMED ward. During this review, diagnoses will be assessed and discussed, eligibility will be confirmed, and a treatment plan will be collaboratively developed. If the lead STATAMED physician approves the admission, a planned admission will be scheduled, specifying the date and time to ensure that the STATAMED ward can prepare for the patient’s arrival and admit him or her without delay.Case manager: Case managers in each STATAMED ward will coordinate interdisciplinary and cross-sectoral treatment planning for the post-discharge period. During the hospital stay, they will participate in medical rounds to support discharge planning. Their responsibilities include assisting patients with urgent social care needs, such as arranging home care services, procuring assistive devices, and securing short-term care home placements. After discharge, case managers will help coordinate necessary therapeutic measures, including organising nursing services, scheduling physiotherapy sessions, arranging home visits by occupational therapists, and making appointments with outpatient physicians. They will also communicate with and involve the patient’s caregivers and relatives as needed. Case managers hold a basic qualification in a medical, therapeutic, nursing, or social care profession (e.g. medical assistants) and have received project-specific training to prepare them for their tasks in the STATAMED trial.Mobile nurses: These nurses will provide follow-up care either at the patient’s home or in a long-term care facility. Their responsibilities include medical tasks such as monitoring vital signs, collecting blood samples for analysis, and performing ultrasounds or electrocardiograms. They also assess patients for functional deficits, provide fall prevention guidance, and report on follow-up care needs. Additionally, mobile nurses can assist with the admission process. If a patient’s regular referring physician is unavailable, the mobile nurse can visit the patient before admission to assess their condition. In such cases, the lead STATAMED physician will be consulted via telemedicine to make the admission decision, and the mandatory referral case review will take place at a later date.

All patients who receive treatment in a STATAMED ward will receive the full set of trial interventions without further differentiation within the intervention group. However, certain services offered by the case manager or mobile nurse (e.g. follow-up care) may not be medically necessary for some patients, may be declined by some patients, or may not be provided due to capacity constraints. All services provided will be documented, and STATAMED staff will also document any requested services that could not be delivered (e.g. due to capacity constraints).

